### Adherence and compliance

The CEMA research center is responsible for preparing the reports for the safety committee to audit the study’s progress. These reports will include the following information: (a) recruitment and follow-up per person per month and comparison with the pre-established goals, (b) adherence of participants (biochemical markers and data on the degree of compliance and a comparison with the objectives foreseen for the exercise groups, (c) quality control (preferences for certain digits, variability, and values out of range), and (d) intermediate and final, primary, and secondary variables for each group and comparisons among groups with respect to the primary variables and other secondary variables. For the interventions with additional exercise, 75% adherence is expected of the 72 planned sessions, along with at least 70% training compliance.

### Data quality

To evaluate the veracity of the data from the questionnaires and from the database, an external personnel team assigned to each group will revise the instruments and questionnaires for a random number of participants. The proposal is to review the data from approximately 25% of the participants in each group, and CEMA members will confirm and certify the validity of the data. The CEMA researchers will create a system to access the study data through a private website (http://www.urosario.edu.co/cema/inicio/), from where authorized researchers can download all the forms, databases, and articles published. For security and privacy, a valid ID and password are necessary to access the data and the forms. This web-based system is used to send data to the data manager. As a quality control measure, the principal study data will be reviewed for features such as a preference for certain figures and data variability. All the forms will be entered in duplicate and they will be checked for inconsistencies and missing data. To minimize potential error, a *Manual of Operations* has been drafted. Until the end of the trial, personnel from the groups will have access to all the information from the trial, except for the statisticians and the safety committee.

### Statistical analysis

The final data will be analyzed using IBM SPSS 22.0 (SPSS, Inc., Chicago, IL, USA) and SAS software (SAS Institute Inc., Cary, NC, USA). An exploratory analysis will be performed to determine the frequency, range, variability, and distribution type for each variable to establish the most appropriate statistical test when comparisons are necessary. These analyses will assess the primary outcome (hepatic fat) and will be undertaken using the intention-to-treat principle. The intention-to-treat analysis for this study will include all participants, including those who are not fully compliant and those with missing outcome data.

Because this is an experimental design with the primary and secondary outcomes measured twice, the first at baseline (*t*_0_ = 0 months) and the second after the interventions (*t*_1_ = 6 months), for four study groups, a comparative analysis between the measurements will determine the differences. A linear mixed model with repeated observations will be used for these comparisons, when appropriate, for each dependent variable. Subsequently, a multivariate analysis will be carried out, and the autocorrelation between repeated measures will be taken into account. We will use longitudinal analysis methods, such as a generalized estimating equation approach, to control the differences among measurements at baseline and to incorporate incomplete observations into this analysis. Pearson correlations will be calculated between the maximal values of the primary and secondary outcomes. Finally, we will investigate whether there is an interaction between the two interventions for the primary outcome after 30–40 min of supervised HIPE and LIPE or combined training (HIPE + LIPE). For these analyses, we will include appropriate interaction terms in the models [60]. We plan to report regression coefficients for the interaction terms and their 95% confidence intervals.

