#### High-intensity physical education class

The high-intensity physical education group (HIPE group, *n* = 25) will follow the standard physical education curriculum plus the Physical Activity Intervention on the Obesity of Schoolchildren (in Spanish, the MOVI-2 program), which is based on a socio-ecological model and targets the school, parents, teachers, and children, focusing on increasing physical activity [31]. MOVI-2 includes basic sports games, traditional games, and other outdoor activities such as running, gymkhanas (which consist of different types of competition with obstacles that make the task difficult), lifting, pushing, wrestling, and hauling (http://www.movidavida.org/), for 60-min sessions three times per week for 6 months with an energy expenditure goal of 300 to 500 kcal/session at 75–85% maximum heart rate (HRmax).

For example, the prescribed energy expenditure during exercise for month 1 is 300 kcal session^− 1^:Conveyors game: Exercise energy expenditure is 9.2 kcal min^− 1^ and exercise duration is 100 kcal per session. Dividing by 9.2 kcal min^− 1^ gives 11 min per session.Four corners game: Exercise energy expenditure is 10.8 kcal min^− 1^ and exercise duration is 100 kcal per session. Dividing by 10.8 kcal min^− 1^ gives 9 min per session^.^Stealing handball game: Exercise energy expenditure is 9.4 kcal min^− 1^ and exercise duration = 100 kcal per session. Dividing by 9.4 kcal min^− 1^ gives 10 min per session.

All playground games will be preceded by a 5-min warm up with endurance or resistance games (i.e., the fastest, the clock, iceman, kangaroo race, etc.). The duration and intensity of all playground games sessions will be verified by a downloadable heart rate (HR) monitor (RS 400; Polar Electro Inc., Woodbury, NY) to achieve the prescribed target HR. All activities will be implemented by monitors with technical qualifications in physical activity and sports, or by sport science graduates, specifically engaged and adequately trained for the program. This protocol is applicable for school-aged boys and girls, independent of the level of skill or their physical aptitude, and is a health-oriented program aimed at balanced physical and psychological development.

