#### Low-to-moderate intensity physical education class

The low-to-moderate intensity physical education group (LIPE group, *n* = 25) will follow the standard physical education curriculum. In addition, endurance and resistance games from the MOVI-2 program will be used with a goal to achieve an expenditure of 1500 kcal/week through 60-min sessions, three times per week for 6 months for 300 to 500 kcal energy expenditure per session at 55–75% HRmax:

Frequency: Three times weekly, excluding holidays and vacation periods

Duration: 60 min, structured into 5 min of warm-up, 45 min dedicated to the main training curriculum, and 10 min dedicated to returning to a rest state

Protocol: Each of the sessions will work on activities based on health-related physical fitness (cardiovascular and muscle endurance and flexibility) at an intensity of between 4.0 and 7.0 MET.

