#### Plus group

The combined group (*n* = 25) performed the 30-min aerobic training program plus the 30-min resistance training, that involve training program used in both HIPE and LIPE. Each session is developed as described above. Additionally, the standard physical education curriculum was followed. The sum of both interventions should not exceed 1500 kcal/week of energy expenditure. All the study participants in this group will receive a hygiene and dietary management plan that includes educational and nutritional support throughout the study.

After 3 months, the intensity will increase and a different exercise sequence will be used until 6 months of intervention have taken place. The exercise duration will be adjusted to achieve the target average caloric expenditure of 1500 kcal/week. Compliance to the exercise protocol, an essential element of an efficacy study, will be defined as successfully completing >90% of scheduled exercise sessions, maintaining the target exercise HR ± 4 beats min^− 1^ for the prescribed duration of the playground games session. The games proposed for this group are presented in Table 1. It should be noted that diverse variations on the games will be carried out to avoid monotony.

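### The planned HIPE x LIPE interaction on liver fat is confounded with dose, because the combined arm is not both full programs, so its coefficient cannot be read as synergy or antagonism

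*Protocol article*

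**What the plan says.** The Statistical analysis section first plans a linear mixed model for four study groups measured at baseline and 6 months. Last in that section, it says that "we will investigate whether there is an interaction between the two interventions for the primary outcome", labelling the combined arm as HIPE + LIPE. It adds that "we will include appropriate interaction terms in the models" and "We plan to report regression coefficients for the interaction terms and their 95% confidence intervals". The coding of those terms is not given.

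The arms are described elsewhere:

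- **HIPE** (High-intensity physical education class): "for 60-min sessions three times per week for 6 months with an energy expenditure goal of 300 to 500 kcal/session", which is 900 to 1500 kcal/week.
- **LIPE** (Low-to-moderate intensity physical education class): "with a goal to achieve an expenditure of 1500 kcal/week through 60-min sessions, three times per week". The same sentence also gives 300 to 500 kcal per session (900 to 1500 kcal/week). The Abstract gives 300 kcal per session (900 kcal/week).
- **Combined** (Plus group): participants "performed the 30-min aerobic training program plus the 30-min resistance training", and "The sum of both interventions should not exceed 1500 kcal/week of energy expenditure". This section also adjusts exercise duration toward an average of 1500 kcal/week and provides a hygiene and dietary management plan to everyone in the group.

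Adherence and compliance gives one figure, 72 planned sessions, for the interventions with additional exercise. It gives no longer schedule for the combined arm.

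**The concern.** With control, HIPE, LIPE and combined arms, an interaction between the two interventions is most naturally the 2x2 factorial contrast. Under additive effects that contrast is zero only if the combined arm receives both programs in full. Here the combined arm has the session time of one program. Its energy ceiling equals the LIPE weekly goal and the top of the HIPE range. The contrast would then differ from zero even if the programs did not interact at all, simply because each was cut back to make room for the other.

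The stake is a published statement on the primary outcome that one program weakens the other, when the data show only that participants did less of each. The reverse error is also possible: a true synergy could be masked.

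The descriptions also disagree on what is being combined. The Plus group section calls the halves aerobic and resistance training; the Statistical analysis section treats the arm as high plus low intensity. That section also refers to 30 to 40 minutes of supervised training, against 60-minute sessions with a 45-minute main part elsewhere.

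**Working it through.** **Plan's own figure.** The protocol gives no power or precision for the interaction. The planning values below come from Power calculation and sample size: difference 5.0, SD 4.1, 25 per arm, 10% loss. (For a simple two-arm comparison at two-sided 0.025 these values give about 98% power at 25 per arm, not the stated 80%. That is a separate matter and nothing below depends on it.)

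**Weekly energy.** 3 x 300 = 900 and 3 x 500 = 1500 kcal/week. The combined ceiling is 1500. Session time is 30 + 30 = 60 minutes, the same as one single program.

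**Model (assumed).** Let H and L be the reductions in liver fat from full HIPE and full LIPE relative to control. Assume a linear dose response, no interaction, and a combined arm that receives the same share f of each full program. Its reduction is then f(H + L). In terms of liver fat,

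combined - HIPE - LIPE + control = -f(H + L) + H + L = (1 - f)(H + L).

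A positive value looks like antagonism. It is zero if f = 1 or if neither program works.

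**Precision.** SE = SD x sqrt(4/n) = 4.1 x sqrt(4/25) = 1.64. With 22 per arm after 10% loss, SE = 4.1 x sqrt(4/22) = 1.75.

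**Chance that the 95% interval excludes zero.** Noncentral t with 96 degrees of freedom (84 at 22 per arm) and noncentrality bias/SE; for the first row, 5.0/1.64 = 3.05.

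| Single-program energy, kcal/week (HIPE, LIPE in either order) | f | H, L (points) | Bias (points) | 25 per arm | 22 per arm |
|---|---|---|---|---|---|
| 1500 and 1500 | 1500/3000 = 0.50 | 5.0, 5.0 | 5.00 | 85% | 81% |
| 900 and 1500 | 1500/2400 = 0.625 | 5.0, 5.0 | 3.75 | 62% | 56% |
| 900 and 900 | 1500/1800 = 0.83 | 5.0, 5.0 | 1.67 | 17% | 16% |
| 1500 and 1500 | 0.50 | 5.0, 2.5 | 3.75 | 62% | 56% |
| 1500 and 1500 | 0.50 | 2.5, 2.5 | 2.50 | 33% | 29% |
| any | any | 0, 0 | 0 | 5% | 5% |

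The reference value with no bias is 5% (2.5% in each direction).

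**Dietary plan.** If the plan in the combined arm adds a benefit D of its own, the bias in the first row becomes 5.0 - D. At D = 2.5 it is 2.5 points (33%); at D = 5.0 it is zero. The size of D is not known.

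**A replacement contrast also depends on dose.** Combined minus the mean of HIPE and LIPE has SE = 4.1 x sqrt(1/25 + 1/50) = 1.00. With all three arms at 1500 kcal/week and H = L = 5.0, the combined reduction is 0.5 x 10 = 5.0, and the contrast is zero as it should be. With single programs at 900 kcal/week, the combined reduction is 0.83 x 10 = 8.33. The contrast then favours the combined arm by 8.33 - 5.0 = 3.33 points with no benefit of mixing, and its interval excludes zero about 91% of the time.

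**The case against.** A reader might infer that the combined arm receives the dose of one program and that the test will therefore report antagonism. The documents do not support this in full.

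- Equality with one program is exact for session time and at 1500 kcal/week. Against a 900 kcal/week program (Abstract for LIPE, lower end of the HIPE range), the ceiling is 1500/900 = 1.67 times one program. The 85% figure belongs to the most extreme dose reading.
- The bias needs at least one program to work, benefit to rise with dose, and factorial coding. The protocol says only that appropriate terms will be used and cites a reference. Exact coding may properly sit in an analysis plan that is not shown.
- The halves are called aerobic and resistance, so an even HIPE/LIPE split is itself an assumption.
- The dietary plan is stated for the combined arm. Controls are offered education and nutritional counselling, and the HIPE and LIPE sections mention neither. Any added benefit in the combined arm would push the coefficient the other way.

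A reader might also infer that the comparison of mixed with single programs is left untested. That goes too far: the four-group mixed model allows it, although the text does not name it. The 30 to 40 minutes may refer to active game time (the HIPE month-1 example sums to 11 + 9 + 10 = 30 minutes), but the text does not say so.

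These points limit the size and certainty of the bias. They do not rescue the coefficient: an unknown dose ratio and a possible dietary effect are further reasons why it cannot be interpreted.

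**Conclusion.** The point holds as one of confounding. As described, the combined arm is not the sum of both programs, so a factorial interaction coefficient mixes interaction with dose, and possibly with diet. If benefit rises with dose, the dose part biases it toward antagonism. With 5.0-point effects the bias runs from 1.67 points (about 17% chance of an interval excluding zero) to 5.0 points (about 85%), depending on which of the protocol's own energy figures applies. With 2.5-point effects at 1500 kcal/week it is 2.5 points (about 33%), and it is zero if neither program works. These figures rest on a linear dose response, equal shares of each program, factorial coding and SD 4.1 for the analysed outcome. A finding of antagonism is therefore a risk, not a certainty. Severity is should-fix: the analysis is supplementary, but it concerns the primary outcome and would be published as a coefficient with a confidence interval.

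**What to change.** 1. Reconcile the Abstract, the HIPE, LIPE and Plus group sections and Statistical analysis on the content, duration and weekly energy of each arm. This includes aerobic/resistance versus high/low intensity, and 30 to 40 versus 60 minutes. State which arms receive the dietary plan. The investigators must settle which description is correct.
2. While the combined arm is not the sum of both programs, do not interpret a factorial interaction term as synergy or antagonism.
3. Analyse arm as one four-level factor. Report each program versus control, combined versus HIPE, and combined versus LIPE, with confidence intervals (SE of each pairwise difference 4.1 x sqrt(2/25) = 1.16).
4. Use combined minus the mean of HIPE and LIPE as a test of mixing only if step 1 confirms that weekly energy is matched across the three exercise arms.

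The analysis change is a paragraph of wording and needs no new data or participants. Step 1 needs only a decision and consistent text, and the wording should be fixed before the allocation codes are opened.

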## Discussion

The relevance of this project is that the results obtained from the objectives proposed will contribute to our understanding of the links between excess weight and alterations in hepatic and adipose metabolism. Moreover, we may be able to identify biomarkers for metabolic abnormalities associated with central obesity that are involved in the induction of oxidative dysfunction processes via lipotoxicity, which is common in physical inactivity and obesity, such as pathologies related to the cardiometabolic system. The study of biomarker profiles in adolescents with metabolic syndrome and obesity compared to a normal weight population could assist in the early diagnosis of cardiovascular diseases. Future studies are warranted to verify the relevance of the biomarkers associated with obesity and elucidate the underlying biochemical processes.

Currently, the management of overweight conditions and public information on the topic have focused on treatments such as caloric restriction, physical exercise, and different drugs. There have been promising results, due to the distinct metabolic adaptations that can prove beneficial for individuals with excess weight. Thus, our research hypothesis is that some physical exercise programs will generate a higher reduction of fat in liver than other interventions. In addition, there may be improvements in the hepatic metabolism and cardiovascular health of overweight/obese adolescents from the district of Bogotá.

At a clinical level, interventions to prevent excess weight and sedentary habits are very costly and the results in the pediatric setting are discouraging and not very cost-effective [60–62]. Hence, our research seeks to evaluate the impact of the interventions, and whether they are easy to implement, safe, economic, and free of secondary effects. The research focuses on assessing hepatic metabolic activity (fat content, as a primary outcome) and bodily composition, blood pressure, insulin sensitivity, lipid and carbohydrate metabolism, and physical condition (secondary outcomes), which are highly relevant.

### Dissemination

We will disseminate the results of our study via presentations at international conferences and articles in peer-reviewed journals. The study will be implemented and reported in accordance with the SPIRIT guidelines (Standard Protocol Items: Recommendations for Interventional Trials) [67] (Additional file 2).

### Future directions

In the short term, this project offers the opportunity to obtain detailed measurements of body composition, cardiometabolic health, and hepatic function in overweight children and adolescents. It will yield information on the effects of physical exercise on them. In the long term, we expect that the results obtained will deepen our knowledge of the effects of supervised physical exercise in the school environment on some of the most frequent metabolic disorders, as well as validate strategies that promote actions aimed at mitigating the risk of the occurrence of these disorders and reducing morbidity. Both of the latter are seen as priority problems by the Ministry of Health and Social Protection. Our work lies within the normative framework for generating preventive alternatives and effective therapeutics described in Colombia’s Integral Health Information System and the Public Health Surveillance System.

### Trial status

The recruitment of adolescents started in January 2018 and will continue through the end of December 2018.

## Abbreviations

A1AT: Alpha-1 antitrypsin
BDNF: Brain-derived neurotrophic factor
BMI: Body mass index
CEMA: Centre for Studies of Physical Activity Measurements (in Spanish)
cIMT: Carotid intima-media thickness
DEXA: Dual-energy X-ray absorptiometry
ECG: Electrocardiogram
EDTA: Ethylene diamine tetraacetic acid
HbA1c: Glycohemoglobin
HDL-C: High-density lipoprotein cholesterol
HIIT: High-intensity interval training
HIPE: High-intensity physical education
HOMA-IR: Homeostatic model assessment of insulin resistance
HOMA-β: Homeostatic model assessment of pancreatic β-cell function
HR: Heart rate
HRmax: Maximum heart rate
LDL-C: Low-density lipoprotein cholesterol
LIPE: Low-to-moderate intensity physical education
MET: Metabolic equivalent
MICT: Moderate-intensity continuous training
MOVI-2: Physical Activity Intervention on the Obesity of Schoolchildren (in Spanish)
NAFLD: Non-alcoholic fatty liver disease
NT: Neurotrophin
